## 2) Objectives\*

The goal of the proposed application is to evaluate in an effectiveness-implementation type I hybrid trial, an enhanced version of eHealth Familias Unidas for reducing depressive, anxious symptoms and suicide behavior in Hispanic youth. Using a randomized rollout design of 18 clinics, the study's aims are to:

**AIM 1:** Evaluate the effectiveness of eHealth Familias Unidas for Mental Health in preventing/reducing depressive, anxiety symptoms; suicide ideation and behavior; and drug misuse among those with poor family communication, elevated levels of depressive or anxiety symptoms, or a history of suicide ideation or behavior.

**H1:** eHealth Familias Unidas for Mental Health will be effective, relative to standard of care, in reducing these outcomes in Hispanic adolescents over time.

**AIM 2:** Determine whether intervention effects are partially mediated by family communication and externalizing behaviors, including drug misuse, and moderated by parental depression.

**H2:** Intervention effects on mental health outcomes will be partially mediated by improvements in family communication, externalizing behaviors (including drug misuse) and moderated by parental depression.

**Exploratory AIM 3:** Intervention impact on mental health and drug misuse as well as sustainment of the intervention in clinics will vary by quality of implementation at clinic and clinician levels.

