#### 4) **Inclusion and Exclusion Criteria\***

Families will be screened based on the following inclusion criteria:

- (a) Female and male adolescents, who self-identify as Hispanic (or Latino(a))

- (b) Adolescent between the ages of 12 – 16 years
- (c) Adolescent living with an adult primary caregiver who is willing to participate
- (d) Families must have broadband internet access on a device, including (but not limited to) a smartphone, iPad, tablet, computer at their home or other location (e.g., school, library, etc.)
- (e) Families screening positive on poor family communication (a score of less than 75 on the communication measure; see measures) or youth reporting elevated depressive or anxiety symptom scores or a history of suicide behavior (ideation or attempts)

Exclusion criteria: Families reporting plans to move out of the South Florida area during the study period.

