mechanism by which to ensure secure access and confidentiality for participants. Each participant will be assigned a unique log-in name and password, which will provide them access to the eHealth Familias Unidas Mental Health session. The log-in procedure will also facilitate the close monitoring of participants, particularly as it relates to session participation rates. Specifically, the log-in procedure will be utilized to record who (i.e., which participant), when (i.e., day/time), how long (e.g., time of session attendance), and for what purpose (e.g., which session) the intervention website was accessed.

Our information technology team employs the latest technology to ensure security and confidentiality of participants, including but not limited to data error checking through forms, filtering output, and the use of encryption. Server Port Hardening will be implemented to keep the web server safe from intrusion. Additionally, a Secure Socket Layer Encryption certificate will be issued to help prevent Internet fraud. The implementation of SSLs (i.e., cryptographic protocols) aims to enhance security over the Internet. IT will conduct stringent testing of web applications prior to the implementation of eHealth Familias Unidas Mental Health to prevent any exploits from occurring and to ensure the confidentiality of participants.

-All participants will not receive the intervention. Participants will receive the intervention depending on when the clinics offer the program, which is based on the study's randomization. After the intervention is complete, assessors will call the families to return to complete follow up assessments. The follow up assessments will occur online through links emailed via REDCap.

The follow up assessments collect the same data as the baseline assessment. All measures will be self-report. We will ask participants to give us the names and telephone numbers of three people who will always know how to reach them, in case we lose contact. We will never share anything participants tell us with these people.

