For mediation analyses, we will use the “product of coefficient” approach that we used in previous analyses to test for an indirect effect of improved family communication by 3 months, decreased externalizing behaviors by 6 months, and further decreased depressive and anxious symptoms as well as suicide ideation and attempts by 18 months. We analyze this in 2 parts, with family communication affecting externalizing followed by externalizing behaviors affecting depressive symptoms. For the second model, the product of the effect of family communication on intervention (a coefficient) and depression on family communication controlling for intervention (b coefficient) measures this latter indirect effect. We will use *Mplus* to compute bootstrapped confidence intervals since this product has a very non-normal distribution. Similarly, we will examine whether externalizing behaviors (including drug misuse) change by 6 months mediates the 18-month depressive, anxious, and suicide behavior outcomes. In addition, we propose to test whether the slope of externalizing behaviors changes on 18-month outcomes as well. To examine moderation by parental depression, we will test for an interaction with that symptomatology at baseline and intervention, both in growth models and in 18-month outcomes. We hypothesize that Familias Unidas’ effects will be moderated by parental depression with the intervention being less effective in preventing/reducing depressive, anxiety symptoms; suicide ideation and behavior and drug misuse when parents have higher depressive symptoms. Parental depression can significantly impair a person’s ability to parent as well as their family functioning and past prevention programs have found that parent depression moderates preventive intervention effects in this manner.

**Exploratory AIM 3:** Intervention impact on mental health and externalizing behaviors, including drug misuse, as well as sustainment, will vary by quality of implementation at the levels of clinic and clinician.

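### The b path for family communication names intervention as its only covariate, so baseline differences between youths can create or hide a mediated effect in Aim 2

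*Protocol*

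**What the plan says.** H2 in section 2 (Objectives) is about change: "Intervention effects on mental health outcomes will be partially mediated by improvements in family communication". Section 7, AIM 2, repeats that aim, proposing "to test for an indirect effect of improved family communication by 3 months, decreased externalizing behaviors by 6 months" and then lower symptoms by 18 months.

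The estimator is then written out. The first factor is "the product of the effect of family communication on intervention (a coefficient") and the second is "depression on family communication controlling for intervention (b coefficient) measures this latter indirect effect". Neither regression names a baseline value of communication, externalizing behavior or symptoms. The product is tested with bootstrapped confidence intervals because its distribution is not normal.

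Two features limit how far this wording reaches:
- The two-part scheme is introduced as a chain, "with family communication affecting externalizing followed by externalizing behaviors affecting depressive symptoms", yet the coefficients that follow are written for communication and depression.
- The externalizing mediator is described as change: "we will examine whether externalizing behaviors (including drug misuse) change by 6 months mediates the 18-month depressive" and other outcomes. Its slope is to be tested as well.

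Baseline values are available. Section 5 (Intervention conditions) states: "The follow up assessments collect the same data as the baseline assessment".

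**The concern.** Clinics are randomized to rollout times, but a youth's level of communication at 3 months is not randomized. It partly carries forward the baseline level, and 18-month symptoms partly carry forward baseline symptoms. If the two are associated at baseline, the b coefficient is non-zero even when improving communication does nothing for later symptoms. The Protocol's own Background (section 3) describes such an association: communication is negatively related to internalizing and externalizing behavior, and is a protective factor for these symptoms.

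The entry rule in section 4 complicates this. Criterion (e) admits "Families screening positive on poor family communication" or youths with elevated symptoms or a suicide history. Selecting on any one of several conditions pushes the communication-symptom correlation upward among those enrolled, from negative towards zero or above. The direction of the bias therefore cannot be assumed.

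Earlier trials of the program improved communication, so a non-zero a path is expected and the Aim 2 conclusion then depends mainly on b. Bootstrapping corrects the shape of the product's distribution, not a b estimate centred on the wrong value.

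**Working it through.** **The plan's own figures.** Under Power Analyses, the mediation test has 64% power if each path has 80%, and 72% if each has 85%. Both reproduce as products: 0.80 × 0.80 = 0.64 and 0.85 × 0.85 = 0.7225. They are arithmetically right, but they presuppose a valid test of b.

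**Inputs.**
- From the Protocol: N = 468; Type I error 0.05.
- From the Protocol, an earlier trial in section 3: 18.8% with poor communication.
- Assumed: two-sided testing; 234 youths per condition; stability of communication s_M = 0.6 and of symptoms s_Y = 0.5; baseline correlation r = 0 to -0.4; intervention effect on communication 0.28 SD; symptom entry cut-off at the top 20%.

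Clinic clustering and calendar time are ignored.

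**Model.** With T the condition and all scores standardized,

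M3 = s_M·M0 + a·T + error, and Y18 = s_Y·Y0 + b·(M3 − s_M·M0) + error.

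Regressing Y18 on M3 and T only, without entry selection, gives on average

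b(as written) ≈ s_M·s_Y·r + b·(1 − s_M²).

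**True b = 0, no entry selection, by hand.** The standard error of b is about 1/√468 = 0.046. For the a path, z = 0.28·√468/2 = 3.03, so its power is Φ(3.03 − 1.96) ≈ 0.86. False rejection of the product is roughly the a-path power times the chance that b appears significant.

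| r | bias 0.6 × 0.5 × r | z | Φ(z − 1.96) | × 0.86 | simulated as written |
|---|---|---|---|---|---|
| -0.2 | -0.06 | 1.30 | 0.25 | 22% | 24% |
| -0.3 | -0.09 | 1.95 | 0.49 | 42% | 43% |
| -0.4 | -0.12 | 2.60 | 0.74 | 63% | 64% |

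Adjusting both equations for M0 and Y0 gives about 4%. A second set of simulations, with a = 0.4 SD and both stabilities between 0.4 and 0.6, gives 12% to 89% as written over the same correlations and 3% to 6% adjusted. At r = 0 the test as written keeps its level (5% to 6%).

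**A true effect can be hidden.** With both stabilities 0.6, r = +0.3 and true b = -0.2, the formula gives 0.36 × 0.3 − 0.2 × 0.64 = 0.108 − 0.128 = -0.020. The simulated mean is -0.019. Power with a = 0.4 SD is 6% as written and 99% adjusted.

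**Either/or entry, imperfect screen.** Let the screen correlate 0.7 with the analysed baseline scores, with population r from -0.2 to -0.4 and a = 0.28 SD. With true b = 0, false rejection as written is about 5% to 9%. With true b = -0.15, power is about 27% to 72% as written, against 79% to 83% adjusted.

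**Raw change does not solve it.** Using M3 − M0 with T only, the coefficient under true b = 0 is (s_M − 1)·s_Y·r / [2(1 − s_M)] = −s_Y·r/2. With s_Y = 0.6 and r = -0.3 this is +0.09 (simulated 0.090), the wrong sign. Without selection, and over r = -0.2 to -0.4 in the second set, false rejection is 16% to 67%. For a mediator positively related to symptoms, such as externalizing behavior, the sign reverses but the mechanism is the same.

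**The case against.** The strongest reply is that controlling for intervention is simply how b is defined in the product-of-coefficients method, not a closed list of covariates. The Protocol nowhere says that baseline values are left out. It refers to earlier analyses and to a Clinical Trials Section 4B that is not shown, and covariate lists are often left to the analysis plan. This stands in part: exclusion of baseline covariates cannot be claimed. But the Protocol does write out the regression with its conditioning variable. In the same paragraph it names baseline where it wants it, for parental depression as moderator. Correcting a stated model differs from asking for missing detail.

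Three stronger readings are tempting and are not supported:
- **That the flaw covers every Aim 2 mediator as written.** The quoted coefficients are for communication. Externalizing is planned as change and as slope; only raw change was examined here, not the slope.
- **That the test merely asks whether mediator and symptom levels are correlated.** The product also needs a non-zero a path, and b is conditional on condition.
- **That the trial is likely to show harmful mediation.** In simulations with true b = 0, rejections in the harmful direction reach 64%/45%/23% (r = -0.2/-0.3/-0.4) only if the screen equals the analysed scores and there are two entry routes. Two further symptom routes (assumed) bring this to 24%/12%/3%. Screen correlations of 0.5 for communication and 0.8 for symptoms (also assumed) bring it to 3%/1%/0%. Section 5 has parents answer the communication screen, whereas the measure is reported by both parents and youths, so a perfect screen is unlikely.

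Also, 85% power per path is a conditional illustration in the Protocol. The 0.28 SD effect is an assumption here that roughly matches it, not a planned value.

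**Conclusion.** The concern holds for the communication path. As worded, b names no baseline covariate and does not isolate the improvement that H2 is about. Randomization does not protect it, and the entry rule makes the direction of the bias uncertain.

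The size is conditional. Without entry selection, false rejection runs from about nominal at zero baseline correlation to about 24% to 64% at -0.2 to -0.4, against about 4% adjusted. With either/or entry through a screen correlating 0.7, false rejection is modest (about 5% to 9%) and the main cost is power, about 27% to 72% against about 80% for a true b of -0.15. These figures rest on assumed correlations, stabilities and cut-offs, and on an individual-level model.

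Only the Aim 2 mediation conclusion is at stake. A reader might infer that the effectiveness result is compromised too; it is not, because the Aim 1 growth-model comparison of conditions does not use this regression.

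**What to change.** In section 7, AIM 2, replace the stated a and b regressions for communication with:
- a path: mediator at follow-up on intervention, baseline mediator and baseline outcome;
- b path: 18-month outcome on mediator, intervention, baseline mediator and baseline outcome.

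Use the same baseline adjustment for the externalizing and drug-misuse mediator in place of an unadjusted change score, and bootstrap the product from these adjusted models. State that b remains observational: adjustment removes only the baseline confounding that these variables measure.

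While editing, make the coefficients of the second model match the externalizing-to-symptoms step it is introduced as. Also reconcile the communication time point, which is 3 months in the analysis text and 6 months in the power example.

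The cost is a few sentences and two extra covariates per equation. The measures are already collected at baseline.

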## 5) Procedures Involved\*

**Design.** To evaluate eHealth Familias Unidas Mental Health in an effectiveness-implementation hybrid Type 1 trial, this study will use a rollout design, which is an extension of a Stepped Wedge design. We will balance, and then randomize all 18 sites into five cohorts of 4 or 3 clinics to when they would end their control phase, when they would begin receiving eHealth Familias Unidas Mental Health, and when they would start the sustainability period where UM staff would no longer provide formal support (i.e., clinical supervision) to the clinic to deliver eHealth Familias Unidas Mental Health. This design is an extension of a Stepped Wedge design since it has three conditions (as shown in the figure) and provides both within and between clinic comparisons of effectiveness over time. Youth and parents will be assessed at baseline, 3-, 6-, and 18-months post-baseline. We will collect electronic health record data (e.g., exposure to an antidepressant) for participants during their control phase.

**Participants.** The sample will consist of 468 Hispanic female and male adolescents and their primary caregivers recruited from one of 18 primary care clinics, who meet the inclusion/exclusion criteria below. We will include a mix of naive and previously involved clinics in the proposed study. Because we did not attempt to institutionalize eHealth Familias Unidas in earlier involved clinics, we do not anticipate much difference in effect, but we will test for this.

A document to assess for the inclusion/exclusion criteria will be included as part of the patient check-in process. We will screen parents and adolescents separately to verify the inclusion and exclusion criteria. Adolescents will be asked questions regarding their mental health (reporting elevated depressive or anxiety symptom scores or a history of suicide behavior) and parents will be asked questions related to communication with their adolescent.

**Recruitment.** Participants will be recruited from 18 primary care clinics.

[figure not shown]

The sites are heterogeneous and consist of federally qualified health centers, academic primary care clinics located within the University of Miami's Health District, and private community clinics. Collectively, these sites jointly serve over 10,000 Hispanic between the ages of 12 -16 per year. Therefore, we do not anticipate any challenges in recruiting 468 youth over the 18-month recruitment period.

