For continuous measures of depressive and anxious symptoms and drug misuse, we will analyze impact using growth modeling with four time points modeled as a multivariate normal distribution. For suicide behavior (i.e., ideation and attempt), and drug misuse, we will conduct generalized growth modeling with mixed effects using these repeated binary measures. For both continuous and binary outcomes, our analytical procedures will follow those we have used previously to analyze Familias Unidas trial data. For our standard analyses we will use *Mplus* to examine changes in growth using its two-level modeling of clinic and individual, commonly called three-level modeling in the mixed effect modeling literature (individuals with repeated measures nested within clinics,). Since youth are recruited from all 18 clinics both during Control and eHealth Familias Unidas Mental Health, we can consider clinic to be a “blocking

factor,” so the overall effect is essentially a mean of the differences in response across all 18 clinics. After suitable transformation of the time axis, handling of missing data, and model fit checking (see Clinical Trials Section 4B for additional details), we will use a Wald type test on the difference in mean slope parameters for eHealth Familias Unidas versus Control assigned participants. Base rates for suicide attempts are low and thus we accounted for them in our analytic plan and power analyses (see below). In a universal trial of Familias Unidas, found that at baseline 9.2% of youth reported suicide ideation and 5.7% reported a suicide attempt in the preceding year. We have presented power analyses below based on these low but not insignificant rates. Finally, to ensure that our final timepoint which has a longer time gap does not overly influence the findings, we will examine transformations of the time axis.

**AIM 2:** Determine whether intervention effects are partially mediated by family communication and externalizing behaviors, including drug misuse, and moderated by parental depression.

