**Power Analyses:** For continuous effectiveness outcomes, such as the slope of depressive symptoms over the 18 months, we have 87% power to detect an effect size of 0.5 (Type I error 0.05), which is the median effect size we found in a previous synthesis project investigating reduced depressive symptoms in 19 prevention programs with a two year follow-up (see Figure 5 in the following reference). We expect this effect size given that we are now including youth who are elevated on depressive or anxiety symptoms or have a history of suicide ideation or attempts. For suicide ideation, our growth models for repeated binary measures indicates we will have over 70% power to detect a yearly odds ratio (OR) reduction of 0.50 when the prevalence of ideation at baseline is 0.12 (or 12%). For suicide attempts, the baseline prevalence we have observed previously is 0.086 (or 8.6%), and this provides 55% power to detect an OR of 0.5. These ORs and prevalence rates were taken from our most recent Familias Unidas trials using the subset of youth with poor family communication, matching our inclusion criteria. For suicide attempts, if we obtain an OR of 0.4, we would have 71% power to detect this change from baseline for attempts and 88% power for ideation. We will analyze impact on K-CAT MDD as well as use missing data and a two-stage design to calibrate these findings against K-SADS MDD, see section 4.4.). Thus, we have sufficient power to detect a large effect on suicide outcomes over time. For the power of detecting a mediation effect, we take as an example 6-month family communication mediating 18-month depressive symptoms. If both the a and b estimators have 80% power of rejecting their nulls, then the product has a 64% power of rejecting the mediation pathway as being significant. If each a and b estimators have 85% power, the product has 72% power of rejection. Additional details are provided in Clinical Trials Section 4B.

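### The added test of the externalizing slope on 18-month outcomes has no stated window; on its natural reading the slope includes the outcome visit and cannot count as mediation evidence for H2

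*Protocol*

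**What the plan says.** Section 5 of the protocol sets the visits: "Youth and parents will be assessed at baseline, 3-, 6-, and 18-months post-baseline". Under the intervention conditions it adds that "The follow up assessments collect the same data as the baseline assessment", so externalizing behaviour is also measured at 18 months.

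The Aim 2 text in section 7 lays out an ordered chain: family communication by 3 months, externalizing behaviour by 6 months, mental health outcomes by 18 months. In line with that order it tests whether externalizing "change by 6 months mediates the 18-month depressive, anxious, and suicide behavior outcomes". It then extends the analysis: "we propose to test whether the slope of externalizing behaviors changes on 18-month outcomes as well". No window is given for this slope.

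Two other places in section 7 show what a slope means in this protocol. The Aim 1 analysis describes "growth modeling with four time points modeled as a multivariate normal distribution", and the power paragraph refers to the "slope of depressive symptoms over the 18 months".

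**The concern.** H2 is a claim about mechanism: the programme lowers externalizing behaviour, and this in turn lowers depressive and anxious symptoms and suicide behaviour. A mediation test supports that claim only if the mediator is fixed before the outcome. The 6-month change meets this condition. A slope that runs to 18 months does not, because one of its four data points, and the most influential or nearly the most influential one, is collected at the outcome visit.

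Suppose the programme lowers 18-month depression directly, and youth who are less depressed at 18 months also score lower on externalizing at that visit, through reverse influence or shared reporting on the day. The externalizing slope then differs between arms and also correlates with the outcome within arms. That pattern is what a product-of-coefficients test reads as mediation, although externalizing behaviour carried none of the effect.

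**Working it through.** **Inputs from the protocol.** Visits at 0, 3, 6 and 18 months (section 5); externalizing measured at each; growth models with four time points (section 7, Aim 1). The protocol states no figure for the weight of each visit in a slope, so there is none to reproduce.

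**Step 1: share of the 18-month visit, linear months.** The information on a straight-line slope is Sxx = Σ(t − mean)², and the share of visit j is (t_j − mean)²/Sxx.
- Mean = (0 + 3 + 6 + 18)/4 = 6.75.
- Deviations: −6.75, −3.75, −0.75, 11.25.
- Squares: 45.56, 14.06, 0.56, 126.56; Sxx = 186.75 before rounding.
- Share of the 18-month visit = 126.56/186.75 = 67.8%.

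**Step 2: transformed axes.** Aim 1 foresees a transformation of time but gives no form, so the forms below are assumptions.

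| Time axis | 18-month share |
|---|---|
| months | 68% |
| log(1 + t/3) | 52% |
| square root | 49% |
| visit number | 45% |
| log(1 + t) | 42% |

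The overlap persists on every axis.

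**Step 3: would a slope that stops at 6 months be a separate test?** For 0, 3 and 6 months the mean is 3, the deviations are −3, 0 and 3, and Sxx = 18. With complete data the least-squares slope is (−3·y0 + 3·y6)/18 = (y6 − y0)/6. This is the change by 6 months divided by a constant, which the Aim 2 text already tests. It keeps 18/186.75 = 9.6% of the linear slope information. The slope test is offered as an addition, so the redundancy is a further reason to read its window as 0–18 months.

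**Step 4: consequence when there is no mediation.** All settings here are assumptions:
- 400 youth in two equal groups (400/468 = 85% of the planned sample), with clinics ignored;
- a direct effect of −0.5 SD on 18-month depression;
- half of the externalizing variance stable within a youth;
- 18-month externalizing raised by 0.2, 0.3 or 0.5 SD per SD of 18-month depression, with no effect of externalizing on depression at any visit;
- a least-squares slope per youth, mediation declared when the a and b paths are both significant, 2,000 replicates.

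| Same-visit effect | False mediation, linear axis | False mediation, log(1 + t) axis | Apparent share mediated, linear axis |
|---|---|---|---|
| 0.2 SD | 21% | 14% | 5% |
| 0.3 SD | 39% | 27% | 11% |
| 0.5 SD | 71% | 54% | 25% |

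Repeat runs move these rates by a few percentage points. A slope from 0, 3 and 6 months is declared a mediator in about 0.3% of the same trials.

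**The case against.** **The window is inferred.** The sentence is loosely worded, does not use the word mediate and names no window. The four-time-point description is written for the Aim 1 outcomes, and the power paragraph sends the reader to a further section (4B) that is not part of this document. This stands: 0–18 months is an inference. It is a strong one, because no other slope window appears in the protocol and a 0–6 month slope would repeat the preceding test.

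**The plan already worries about the last visit.** Aim 1 says that time-axis transformations will be examined so that the late visit does not dominate. This stands as to size. A reader might infer that two-thirds of the slope always comes from the outcome visit, but that holds only for untransformed months. It does not answer the point, because a transformation changes the weight of the 18-month value and not its place in time.

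**Not all externalizing data come from the youth.** The measures include a parent-reported checklist (RBPC) beside the youth self-report (YSR). For the parent report, shared reporting by one person does not apply directly. Same-visit overlap and reverse influence still do.

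**The error rates rest on assumed effects.** The 0.2–0.5 SD range and the 50% stable variance have no source in the protocol, and the simulation uses a joint-significance test where the plan names bootstrapped intervals in Mplus. The rates therefore show how large the problem could be and do not predict what this trial will find.

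**Conclusion.** The point holds in a limited form. The plan adds a slope test to the H2 mediation analysis without a window, and on the natural reading the slope shares its most informative visit, or nearly so, with the outcome. That breaks the 3–6–18 month ordering that the plan sets for itself. The 18-month visit supplies about 68% of the slope information on a linear axis and about 42–52% on the transformed axes tried. Under the assumed same-visit effects of 0.2–0.5 SD with no true mediation, a positive result appears in about 21–71% of trials on a linear axis and 14–54% on a log axis.

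A reader might go further and infer that the Aim 2 mediation analysis as a whole is unsound. The protocol does not support that. The test of externalizing change by 6 months against 18-month outcomes is correctly ordered, and nothing says that the slope result alone would establish H2. Only the additional test is affected.

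**What to change.** Add one sentence to the Aim 2 analysis: the externalizing slope is estimated over 0–18 months, is reported as a parallel-process association with the 18-month outcomes, and does not count as evidence of mediation. H2 for externalizing behaviour then rests on the time-ordered test already listed.

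Restricting the slope to 0, 3 and 6 months is not a useful replacement, since by Step 3 it reproduces that listed test.

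No new data or visits are needed. The cost is that one fewer analysis can support H2.
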